# Hwangryunhaedoktang in adult patients with Atopic Dermatitis: a randomised, double-blind, placebo-controlled, two-centre trial - study protocol

**DOI:** 10.1186/1472-6882-11-68

**Published:** 2011-08-23

## Abstract

**Background:**

Atopic Dermatitis is a chronic relapsing eczematous skin disease with increasing prevalence and rising costs. It has a clear impact on a patient's quality of life. Many patients are worried about the use of usual care techniques, such as corticosteroids and antihistamine due to the widespread fear of adverse effects. Complementary and alternative medical approaches have been employed to relieve symptoms of Atopic Dermatitis. Hwangryunhaedoktang is among the most strongly preferred and widely used herbal medicines for Atopic Dermatitis in Korea, as it causes very few serious adverse effects.

We aim to establish basic clinical efficacy and safety data for Hwangryunhaedoktang, which is approved as an herbal medication by the Korean Food and Drug Administration, in adult patients with Atopic Dermatitis.

**Methods/Designs:**

This study is a randomised, double blind, placebo-controlled, two-centre trial with two parallel arms (Hwangryunhaedoktang and a placebo). The diagnosis of Atopic Dermatitis will be made according to the criteria of Hanifin and Rajka by two different Oriental medicine doctors. We will include participants experiencing typical conditions of intermittent or continuous Atopic Eczema for six or more months. Participants will receive Hwangryunhaedoktang or a placebo-drug for eight weeks. The total duration of each arm is eleven weeks. Each participant will be examined for signs and symptoms of Atopic Dermatitis before and after taking medication. A follow-up to evaluate the maintenance of safety will be performed two weeks after the final administration of medication.

**Discussion:**

This trial will utilize high quality trial methodologies in accordance with consolidated standards of reporting trials guidelines. It will provide evidence for the clinical efficacy and safety evaluation of Hwangryunhaedoktang in adult patients with Atopic Dermatitis. Moreover, we will also employ health-related quality of life questionnaires to assess the changes in quality of life.

**Trial registration:**

Current Controlled Trials ISRCTN26218532

## Background

Atopic Dermatitis (AD) is a chronic inflammatory pruritic skin disease that is often associated with other atopic disorders such as allergic rhinitis and asthma[1]. It is characterised by poorly defined erythema with oedema, vesiculation, and weeping in the acute stage and skin thickening (lichenification) in the chronic stage[2]. These irritating symptoms result in a severely reduced quality of life (QOL). In particular, itching that continues throughout the day and worsens at night causes sleep loss and impacts everyday activities and psychosocial well being [3,4].

The prevalence of AD has doubled or tripled in industrialised countries during the past three decades; 15% to 30% of children and 2% to 10% of adults are affected[5]. Childhood disease continues into adulthood in a significant number of individuals and represents a notable burden[6]. AD should be regarded as a condition that has the potential to be a major handicap involving considerable personal, social and financial consequences both for the family and for the community[7].

The most common therapies for the treatment of moderate and severely relapsing AD are topical corticosteroids, emollients, oral antihistamines, antibiotic agents, immunosuppressive agents, or non-pharmacologic approaches[2]. However, these methods do not ensure successful treatment in every patient with AD. Oral corticosteroids improve the lesions of AD, but a disease flare may occur when these medications are stopped. In addition, the local and systemic side effects of topical steroids, such as skin atrophy, hypo-pigmentation, adrenal suppression, cataracts, glaucoma, and growth retardation, are well recognised[8]. Although pruritus can be treated with antihistamines or tricyclic anti-depressants, these agents can affect a child's ability to learn or an adult's ability to drive and work[9].

In this context, various complementary and alternative medicine (CAM) treatments have been administered for AD in clinical practice. Complementary and alternative therapies are commonly used because of concerns about the potentially adverse effects of conventional therapies and frustration with the lack of appropriate regular use[10]. Some studies have reported the effectiveness of acupuncture or herbal medicine, which is the most popular form of CAM therapy, for the treatment of AD when used alone or concomitantly with usual care[10-12]. In the few number of trials that have been conducted, the quality and the small sample sizes of these studies make it difficult to reach firm conclusions concerning these treatments. Well-designed, randomised, controlled trials are needed to examine the efficacy of complementary and alternative treatments for AD.

The purpose of this study is to establish the basic clinical efficacy and safety data for Hwangryunhaedoktang, which is approved as an herbal medication by the Korean Food and Drug Administration (KFDA). The use of Hwangryunhaedoktang for AD is based on the principles of Traditional Korean Medicine (TKM). In this medical tradition, Hwangryunhaedoktang is administered to treat the pattern of wind-heat, blood-heat, or blood deficiency associated with AD[13]. Also, several studies demonstrated that Hwangryunhaedoktang exerts anti-inflammatory, antibiotic, antioxidative, and immunosuppressive activities[14,15]. However, there are no relevant randomised, controlled clinical trials regarding AD.

We will conduct a randomised, double-blind, placebo-controlled, two-centre trial of Hwangryunhaedoktang in adult patients with AD. Because of the absence of a gold standard for the treatment of AD, this trial will be conducted to determine the effectiveness of these herbal medicines by comparison with a placebo controlled group.

## Methods/Design

A randomised, double-blind, placebo-controlled, two-centre trial will be conducted at the Wonkwang University Oriental Medical Centre in Gunpo and at the Sangji University Oriental Medical Centre in Wonju, Korea. Participants fulfilling eligibility criteria will be selected. Enrolled participants will be randomly allocated to two parallel groups: the Hwangryunhaedoktang and placebo arms. Each participant will be examined for signs and symptoms of AD before and after taking medication. A follow-up to evaluate the maintenance of safety will be performed by phone-call (Figure 1).

**Figure 1 F1:**
[figure not shown]
**Study Flow Chart**.

### Recruitment

We will recruit participants by advertisement in local newspapers and on the websites of local medical centres in Gyeonggi-province and Gangwon-province. Respondents will be contacted by clinical trial coordinators (CRC) to determine eligibility via a telephone pre-screen. If an applicant meets the study criteria, he or she will be invited to the clinical research centres and be examined for eligibility. Oriental medicine doctors and Internal medicine doctors will conduct the screening together to improve the quality of eligibility assessment. Oriental medicine doctors will manage the whole process of screening. Internal medicine doctors will assess the complete blood cell count (CBC), erythrocyte sedimentation rate (ESR), blood chemistry, PA chest film, and urine analysis to exclude patients with serious liver and kidney disease.

### Inclusion criteria

Eligible participants of both sexes who are 19 years or older will be enrolled according to the inclusion and exclusion criteria. The diagnosis of AD will be made according to the criteria of Hanifin and Rajka by two different Oriental medicine doctors. We will include participants experiencing the typical conditions of intermittent or continuous Atopic Eczema for six or more months. Participants will be instructed to discontinue other treatments for AD during the run-in, treatment, and follow-up periods. Written informed consent will be obtained from each participant.

### Exclusion criteria

Participants will be excluded if they suffer from serious medical conditions, such as uncontrolled hypertension, diabetes mellitus requiring insulin injection, past or current malignancy, liver or kidney dysfunction, anaemia, active pulmonary tuberculosis, or other severe dermatitis or infectious or systemic diseases incompatible with treatment with herbal medicines. The exclusion criteria are as follows: administration of steroids and immunosuppressants *per os *within one week of interview; the use of other forms of AD treatment except those involving external application; pregnancy, lactation, or the lack of a form of contraception; underlying disease or history of severe hepatic disease, abnormal results for liver function test (greater than twice the upper limit of normal); participation in another clinical trial within one month of enrolment; hypersensitivity or allergic reactions to herbal medicines that are related to this trial; diseases that can affect the absorption of drugs or disordered digestion after surgery related to such a disease; inability to understand written consent or engage in this study due to mental retardation or other emotional or mental problems; or judgment by experts that the potential subject's participation is inappropriate.

Exclusion will be primarily based on the information provided by the patients. Also, additional examinations, such as CBC, ESR, blood chemistry, PA chest film, urine analysis, and vital signs will be performed before the trial to ensure that the patients do not suffer from these diseases. Over-the-counter (OTC) drugs will be allowed for the management of headaches, dyspepsia, etc.; however, participants will be gently advised to reduce the doses, stop taking supplements, or refrain from adding other supplements to their regimen. Some OTC drugs, such as those containing anti-histamine or anti-allergenic agents, will not be allowed, as there are concerns that these drugs might have direct impacts on AD.

These restrictions will be based on the information provided by patients, and researchers will then evaluate whether or not some of these components would impact AD. We will record the drugs taken by each participant at every visit, and participants will be asked to notify us of any changes in their medication/supplement regimen. Additional herbal prescriptions, acupuncture treatments, or therapeutic interventions by other clinicians will not be allowed during the trial period. The complete eligibility criteria are in Appendix 1.

### Sample size

We wished to estimate the sample size that would be sufficient to detect significant differences in the SCORing Atopic Dermatitis (SCORAD) index between the experimental and control groups. Sample size was determined prospectively, as described in a previous study[16,17]. The mean and standard deviation of expected difference scores in SCORAD were 13 and 20 between the experimental and control group. The following formula was used to estimate the sample size for a two-group trial:

$$\frac{2{\left(Z_{\alpha ∕2}+Z_{\beta }\right)}^{2}\sigma^{2}}{{\left(\mu_{c}-\mu_{t}\right)}^{2}}$$

Calculations were performed using 80% power, a 5% significance level, and a 25% dropout rate. The required sample size was approximately 37 participants for each group. We plan to enrol 100 participants in each of the two groups, allowing for a 25% withdrawal rate.

### Randomisation and allocation

The randomisation procedure will be guaranteed by the authorised Clinical Research Organisation (CRO). An expert on statistics from CRO who have no contact with the study participants will conduct the randomisation of participants. Participants will be assigned random numbers via random number generator program (Microsoft Office Excel 2007). Random numbers will be sent to each centre, and randomisation table will be kept blinding by CRO during the research period. Ultimately, 100 participants will be randomised into the two groups at the two centres. However, the number of subjects planned for each location is not fixed. Opaque sealed envelopes containing serial numbers will be delivered to each centre. Opaque sealed randomisation table kept by CRO should be opened as a Standard Operating Procedure (SOP). If it has to be opened in urgent situation dealing with serious adverse events, primary investigator must report that to the CRO. Before the random assignment, all participants will be informed that they would be allocated to one of two groups. Random allocation will be conducted at the second visit. Random numbers with their corresponding participants will be determined by the order of the time of second visit. The allocation results will not be announced to the participants until the last visit of the last randomised participant.

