### Statistical analysis

Analyses will be performed for two populations: 1) an intention-to-treat population consisting of all randomised participants who have at least one measurable outcome report following treatment (missing data are replaced with the last observation values) and 2) a per-protocol population including only participants without major protocol deviations. All data will be descriptively analysed. All main analyses will be based on the intention-to-treat population and conducted using LOCF (last observation carried forward) imputation method. For primary outcome measures, the mean differences from baseline values to the end of treatment will be compared using a independent T-test (Expected noncentrality parameter = 2.87, Critical t = 1.99, Power = 0.80). Paired T-test or non-centrality Wilcoxon rank sum test will be used for comparing safety variables. Repeated measure ANOVA (analysis of covariance) or repeated measure ANCOVA tests will also be performed for within-group and between-group analyses. Baseline data will be collected on each participant at randomisation in trial can be used to describe the population of patients, to assess comparability of treatment groups, to achieve balanced randomisation, to adjust possible comfoundings for prognostic factors, and to undertake subgroup analyses. We will exercise caution when drawing conclusions from subgroup findings.

Statistical analyses will be performed using the STATA statistical package program (ver. 11.0), and the level of significance is established at α = 0.05.

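### The allocation as described uses neither centre nor any baseline variable, yet baseline data are said to help balance the randomisation, and the primary t-test ignores centre

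*Protocol article*

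**What the plan says.** **Allocation (protocol article, Randomisation and allocation).** A CRO statistician produces random numbers in Excel 2007. On distribution the section says: "Random numbers will be sent to each centre, and randomisation table will be kept blinding by CRO during the research period". Sealed envelopes with serial numbers also go to each centre. Allocation takes place at the second visit, and the matching rule is: "Random numbers with their corresponding participants will be determined by the order of the time of second visit". On centre sizes: "However, the number of subjects planned for each location is not fixed". On the total: "Ultimately, 100 participants will be randomised into the two groups at the two centres".

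**Baseline data (Statistical analysis).** Among the things for which data collected at randomisation can be used, the section lists "to achieve balanced randomisation". Adjustment for prognostic factors and subgroup analyses appear in the same list.

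**Primary analysis (Statistical analysis).** Mean change in SCORAD from baseline to end of treatment is compared between arms by an independent t-test. Repeated-measures ANOVA or ANCOVA is named as a further analysis. Centre is not mentioned for any of them.

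**The concern.** The Statistical analysis section attributes to the randomisation a property that the described procedure does not give it. Numbers generated beforehand and taken in order of visit leave no step at which a baseline value could influence the arm. A reader relying on that sentence would think the arms are balanced by design on prognostic factors.

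The primary test does not make up for this. The two centres recruit in different provinces, each enrols an unfixed number, and SCORAD is largely an assessor's rating. If mean change differs between centres and the arms are unevenly spread over them, part of the centre difference enters the unadjusted treatment estimate as chance error. What is at stake is precision and a correct description of the design. The validity of the test is not in question.

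**Working it through.** **1. The two sections side by side.** The allocation rule has two inputs: a random number and the time order of second visits. The data collection schedule (Table 1) puts baseline SCORAD, IgE and eosinophil count at the second visit, the same visit at which allocation takes place. No step in the rule reads these values, the screening data or the centre. The balance wording therefore matches nothing in the described procedure.

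**2. The plan's own figure.** From the Sample size section: difference 13, SD 20, two-sided 5%, 80% power.

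- n per arm = 2 × (1.960 + 0.842)² × 20² / 13² = 37.15. This reproduces the stated figure of about 37.
- With 25% dropout: 37 / 0.75 = 49.3, so 50 per arm and 100 in total.

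This matches the 100 in Randomisation and allocation. The Sample size section itself says "We plan to enrol 100 participants in each of the two groups, allowing for a 25% withdrawal rate", which would be 200. I use 100 in total below.

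**3. Chance of a 60:40 or worse split within a centre.** Centre sizes are not given, so they are assumed. The method of generation is not given either, so two models are shown:

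- simple randomisation: binomial(n, 0.5);
- one list shared by both centres and fixed at 50:50 overall: hypergeometric(100, 50, n).

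| Assumed centre size | Simple | Shared list, 50:50 overall |
|---|---|---|
| 30 | 0.36 | 0.27 |
| 40 | 0.27 | 0.15 |
| 50 | 0.20 | 0.07 |
| 70 | 0.12 | 0.004 |

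With permuted blocks within centre, the difference between arms in a centre cannot exceed half a block (2 patients for blocks of 4), whatever the centre sizes turn out to be.

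**4. Effect on the treatment estimate.** Take two centres of 50 and 50 per arm. The SD of the difference between arms in the share from one centre is √(2 × 0.25 / 50) = 0.10. Multiply by an assumed centre difference D in mean SCORAD change:

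- D = 5: SD of chance error 0.5 points
- D = 10: 1.0 point
- D = 15: 1.5 points

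**5. Precision gained by including centre.** Suppose the SD of 20 already contains the centre spread. Two equal centres that differ by D contribute variance (D/2)².

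- Unadjusted SE = √(2 × 400 / 50) = 4.00.
- D = 5: √(2 × 393.75 / 50) = 3.97.
- D = 10: √(2 × 375 / 50) = 3.87.
- D = 15: √(2 × 343.75 / 50) = 3.71.

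**6. Cost of an uneven overall split.** With 75 completers, power is Φ(13 / [20 √(1/m₁ + 1/m₂)] − 1.96). At 50:50 (37.5 per arm) it is 0.804; at 60:40 (45 and 30) it is 0.787.

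**The case against.** The strongest reply is that a condensed article may leave blocking and stratification to the full protocol, and that its silence on them is no fault. That stands. Several stronger readings are tempting, and the text does not support them:

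- **One unstratified list across both centres.** The section never gives the number of lists, blocks or strata. Numbers and envelopes sent to each centre fit a separate series per centre equally well.
- **Envelopes that cannot follow the visit order.** This would hold only if the order ran across the whole trial. The text does not say so, and order within centre is workable.
- **The unfixed centre split as an error.** It is ordinary open enrolment, and blocking by centre works without fixed sizes.
- **Each centre rating SCORAD with its own staff.** The Blinding section says only that blinded researchers assess outcomes.
- **Bias.** Chance imbalance does not bias the comparison or invalidate the t-test. If the SD of 20 includes centre spread, its effect is already in the standard error.

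Two further replies have some force. The balance wording sits in a generic list of what baseline data can be used for, so it may be no more than loose drafting. An unadjusted t-test is also valid, and covariates are often left to an analysis plan. But the sentence still claims something the described allocation does not do, and the article does fix the primary test, as one without centre.

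**Conclusion.** The point holds as a mismatch between two sections and as an avoidable weakness in the stated primary test. The allocation rule uses no baseline variable and no centre, so the balance wording is unsupported as it stands.

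The statistical cost is modest. The chance error has an SD of about 0.5 to 1.5 points against a target of 13. For a 10-point centre difference, the standard error would fall from 4.00 to 3.87. These figures rest on assumptions that the document does not supply: two equal centres, 100 participants in total, and a centre difference of 5 to 15 points. The imbalance probabilities depend also on whether arm totals are free or fixed. With 200 participants the cost would be smaller still. The change is worth making because it costs almost nothing, and because the randomisation method cannot be altered once allocation is complete.

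**What to change.** 1. In Statistical analysis, replace the primary t-test with a linear model for SCORAD change that includes treatment and centre. Cost: one degree of freedom.
2. In Randomisation and allocation, state that the CRO prepares a separate permuted-block series for each centre, with concealed and varying block sizes, assigned in order of second visit within that centre. If this is already the procedure, say so. Fixed centre sizes are not needed. Cost: the CRO regenerates the list once before the first allocation. Blocks are slightly more predictable than simple randomisation, which varying sizes and blinding contain.
3. Delete the balance wording from the list of uses of baseline data, or reword it to describe what the randomisation actually does. Cost: one sentence.

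If allocation has already begun, items 1 and 3 can still be made before unblinding.

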### Blinding

In this trial, investigators will not be in contact with the CRC, the clinical pharmacist, or the statistician. The success of blinding will be assessed at each participant's last visit. Researchers who are blinded to the allocation results will perform the outcome assessment. The blinding procedure will also be verified by the authorised CRO.

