### Secondary outcome measurement

Secondary outcome measurements include the total IgE and eosinophil counts. These will be measured at treatment initiation, at four weeks after the first medication administration, and at eight weeks after the first medication administration. The EuroQoL 5-Dimension (EQ-5D), the Health Utilities Index Mark 3 (HUI3), and the Dermatology Life Quality Index (DLQI) will be measured at treatment initiation and at eight weeks after the first medication administration, as a measure of health outcomes. The data collection schedule is detailed in Table 1.

**Table 1 T1:** Data Collection Schedule

Period	Screening	Treatment period				Followup
**Visit**	**1st** **(D -7)**	**2nd** **(D 1)**	**3rd** **(D 15)**	**4th** **(D 29)**	**5th** **(D 57)**	**(D 71)**

Informed consent	◯					

Demographic characteristics	◯					

Medical History	◯					

Safety Assessment	◯	◯	◯	◯	◯	

Total IgE, Eosinophil count		◯		◯	◯	

SCORAD Index		◯	◯	◯	◯	

Dermatology Life Quality Index		◯			◯	

EQ-5D		◯			◯	

Health Utilities Index Mark 3		◯			◯	

Adverse effects			◯	◯	◯	◯

Blinding Assessment					◯	

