### Data and safety monitoring

To maintain the quality of this trial, monitoring will be conducted by Pharma CRO, a CRO located in Gyeonggi, Korea. Investigators can also be convened to discuss practical issues that might be encountered, such as dealing with serious adverse events, revising the protocol, and addressing certain important issues that might be raised by investigators and participants.

We defined adverse events as unintended signs, symptoms, or diseases occurring after treatment that were not necessarily related to the intervention. The safety assessment is based primarily on the frequency of adverse events, which include all serious adverse events. Information regarding adverse events will be summarised by presenting the number and percentage of participants experiencing any adverse events. During the trial, all adverse events will be observed in detail and documented in case report forms (CRFs).

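### The release rule lets participants learn their allocation from the last randomised participant's day 57 visit, before the final day 71 adverse-event contacts are complete

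*Protocol article*

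**What the plan says.** The relevant statements are all in the protocol article.

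- **Randomisation and allocation**, on disclosure: "The allocation results will not be announced to the participants until the last visit of the last randomised participant".
- **Randomisation and allocation**, on custody of the code: "randomisation table will be kept blinding by CRO during the research period". The article does not define that period. The section also provides a route for opening the table in an emergency.
- **Blinding**: "The success of blinding will be assessed at each participant's last visit".
- **Table 1** (under Secondary outcome measurement): the row "Blinding Assessment" has a single mark, in the column of the 5th visit, D57. The D71 column is headed as follow-up, carries no visit number, and is marked only for adverse effects.
- **Methods/Design**, opening paragraph: "A follow-up to evaluate the maintenance of safety will be performed by phone-call".
- **Abstract, Methods/Designs**: "A follow-up to evaluate the maintenance of safety will be performed two weeks after the final administration of medication", and "The total duration of each arm is eleven weeks".
- **Data and safety monitoring**: "The safety assessment is based primarily on the frequency of adverse events".

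**The concern.** A rule for releasing allocation should be tied to the end of blinded data collection. Here it is tied to an event that, in the article's own usage, comes before the last scheduled data are in. It also names the last person randomised rather than the last person to finish.

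The data still due after that event are adverse events. They are collected by telephone, so they depend on what the participant says, and adverse-event frequency is the main basis of the safety assessment. Someone who has just learned that they took the herbal medicine or the placebo may report differently at that call. The D71 contact exists only to evaluate safety, so the purpose of the call is what is at stake.

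The custody sentence in the same section adds to the difficulty. If the research period runs through follow-up, the section gives two different earliest points for release. If it ends at D57, nothing in the section protects the D71 contact.

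**Working it through.** **Step 1. What *last visit* means in this article.**

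| Source | What it fixes |
|---|---|
| Blinding section | Blinding success is assessed at each participant's last visit |
| Table 1 | That assessment is marked once, at the 5th visit, D57 |
| Table 1 | D71 is the only column without a visit number |
| Methods/Design | The follow-up is by telephone |
| Patient safety | Vital signs are taken at every visit, which a telephone call cannot do |

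All five agree that the last visit is D57 and that D71 is a later contact, not a visit.

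**Step 2. Reproduce the stated timeline from the Table 1 days.**

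- Treatment: D57 − D1 = 56 days = 8 weeks, as stated.
- End of treatment to follow-up: D71 − D57 = 14 days = 2 weeks, as stated.
- Whole course, D−7 to D71: 71 + 7 = 78 days, or 77 if there is no day 0. 77/7 = 11.0 and 78/7 = 11.1 weeks, matching the stated eleven weeks. The eleven weeks are reached only if the D71 contact is counted.

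**Step 3. The gap.** The earliest permitted announcement is D57 of the last randomised participant. That person's final adverse-event contact is at D71, 14 days later.

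**Step 4. Who is exposed.** On schedule, a participant randomised *t* days before the last one has the D71 contact 14 − *t* days after the earliest permitted announcement. Those with *t* below 14 are exposed, that is, everyone randomised in the final 14 days of accrual.

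**Step 5. How many.** The accrual period is not given. Assume even accrual over *m* months of 30.4 days. The expected number is N × 14 / (30.4 × *m*). The article gives two totals: the Sample size section plans 100 per group (200 in all), while Randomisation and allocation has 100 randomised into the two groups. Both are shown.

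| Assumed accrual | Share | N = 100 | N = 200 |
|---|---|---|---|
| 6 months | 14/182.4 = 7.7% | 7.7 | 15.4 |
| 12 months | 14/364.8 = 3.8% | 3.8 | 7.7 |
| 18 months | 14/547.2 = 2.6% | 2.6 | 5.1 |
| 24 months | 14/729.6 = 1.9% | 1.9 | 3.8 |

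**Step 6. Which data are exposed.** Table 1 ends SCORAD, total IgE, eosinophil count, DLQI, EQ-5D and HUI3 at D57. Adverse effects are marked at D15, D29, D57 and D71. On schedule, only the last of these four contacts can fall after disclosure.

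**Step 7. After the fix.** If release waits for every participant's D71 contact, no scheduled data collection follows it. Sample size, power and significance level do not change.

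**The case against.** The strongest reply is that the sentence sets a floor and not a date. It says when participants may not yet be told, and nothing in the article schedules an announcement at D57. That stands. A reader might infer that the last participants' safety follow-up *is* collected unblinded; the text supports only that it *may* be.

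The second reply is that the custody sentence already protects the D71 contact. The Inclusion criteria section names a follow-up period, and the eleven-week total includes it, so a research period covering follow-up is a natural reading. On that reading the table stays closed until the last D71 contact and there is nothing to announce earlier. This is a fair point, but it rests on a term that the article leaves undefined. If it is right, two sentences in one section give different release points and still need reconciling.

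Three stronger readings are tempting and are not supported:

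- **Assessors or site staff are unblinded.** The sentence concerns telling participants, and the Blinding section has blinded researchers assess outcomes. That a participant might reveal the arm to the caller is possible, but it is conjecture.
- **The primary outcome is exposed.** SCORAD has a self-rated component, and the rule is not tied to completion by everyone. An earlier participant whose 5th visit fell after the trigger could therefore be told before the final SCORAD. This requires a late visit and prompt disclosure, and the article gives no visit windows or late-visit rate from which to size it.
- **The blinding questionnaire is compromised in the last participant** because no order is set against the announcement. This presumes a same-day announcement that the text does not schedule, and the ordering is operational detail that an article may leave to a procedure.

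It is also fair to say that most on-treatment events would already have been recorded at D15, D29 and D57, before any permitted disclosure on schedule.

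**Conclusion.** The point holds as a release rule tied to the wrong event, with small consequences. In the article's own usage the earliest permitted announcement is D57 of the last randomised participant, 14 days before that person's adverse-event contact at D71. The final safety report of the last few participants may therefore be collected after they know their allocation: about 2 to 8 of 100 (or about 4 to 15 of 200) under assumed even accrual over 24 to 6 months. The true accrual pattern is not stated, and faster accrual near the end would raise the number.

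The exposure is confined to one post-treatment contact. The primary analysis and all other efficacy and quality-of-life data are not affected on schedule. The documents give no basis for estimating any change in adverse-event frequency. The correction is worth making because adverse-event frequency is the main safety measure, the rule is stated rather than merely left out, and moving it costs almost nothing.

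**What to change.** In Randomisation and allocation, change the disclosure sentence so that allocation is not announced to participants until every participant, and not only the last randomised, has completed the D71 follow-up contact. Define the research period in the custody sentence so that it runs to the same point; the two sentences then give one release date. Leave the emergency unblinding route as it is.

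The cost is one sentence and a definition. Participants learn their allocation about two weeks later. No visits, staff or participants are added, and the sample size and analysis are unchanged.
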